#### Coroner and paramedic services (Aim 3)

Data-sharing agreements with the Office of the Chief Coroner for Ontario (OCC) and Toronto Paramedic Services (TPaS) will cover both de-identified individual- and aggregated-population level data on the incidence of fatal and non-fatal overdose events, including toxicology, temporal information, and geographic locations.

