#### Longitudinal analysis of time-updated overdose data (Aim 3)

Using OCC and TPaS data, the influence of DCS on the annual incidence of fatal and non-fatal overdose events will be characterized, while adjusting for underlying trends over time. Following others [54], conditional fixed effects Poisson models will be employed to test overdose incidence counts in geographic units that do and do not have DCS present, while adjusting for the presence of SCS. This approach allows for assessment of the estimated effect of DCS by analyzing the fluctuation in incidence rates in areas before and after DCS implementation, and by then comparing the relative change in incidence to other geographic areas. Disentangling the independent effects of DCS from those of SCS presents analytic challenges. However, SCS in Toronto were operational before DCS. This stepwise implementation represents an ideal natural experiment to assess the independent effect of DCS.

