### Limitations

The study has limitations typical of community-based intervention evaluations. Since denying access to DCS is not ethical or feasible, the recruitment process is being integrated directly into the delivery of DCS. While this will allow for the collection of data from a large proportion of the population of DCS clients, it does present limitations. For instance, it is not possible to estimate the number of individuals that will access DCS and provide data, nor the total person-time of data. Second, we note challenges in disentangling the impact of SCS and DCS on overdose incidence and related behaviors given that these two interventions will be co-located in our study setting. However, the 1-year delay between the implementation of SCS and that of DCS provides an ideal natural experiment to test the independent effects of these interventions. Further, the harmonization of data collection tools between SCS and DCS evaluations will further allow for the assessment of independent effects as we are able to evaluate outcomes among SCS clients who do and do not use DCS. Another limitation is the absence of a comparison group, except for the SCS sub-analysis. A final challenge worth noting is that while we would prefer that participants create an anonymous identifier, since this would allow us to link their data from separate visits to DCS and therefore employ panel approaches, this will depend upon the willingness of clients to consent to participating in the research, creating an anonymous identifier, and consistently recording their survey responses under their identifier at subsequent visits.

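### A one-year SCS lead and an SCS presence term do not isolate the effect of DCS: later growth in the SCS effect is credited partly to DCS, and wholly if no SCS-only areas enter the model

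*Protocol article*

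**What the plan says.** In Longitudinal analysis of time-updated overdose data (Aim 3), the article states the target: "the influence of DCS on the annual incidence of fatal and non-fatal overdose events will be characterized, while adjusting for underlying trends over time". On the model it says: "conditional fixed effects Poisson models will be employed to test overdose incidence counts in geographic units that do and do not have DCS present", and it adds "while adjusting for the presence of SCS". It describes no other SCS term.

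The section concedes that "Disentangling the independent effects of DCS from those of SCS presents analytic challenges". It then resolves the difficulty by noting that SCS were running before DCS, and concludes: "This stepwise implementation represents an ideal natural experiment to assess the independent effect of DCS". Limitations makes the same argument and gives the interval: "the 1-year delay between the implementation of SCS and that of DCS provides an ideal natural experiment".

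Three other parts of the article matter here:
- Background and Study partners: there are three DCS sites, all co-located with SCS.
- Spatial patterns of fatal and non-fatal overdose in Toronto (Aim 3): areas with both services are to be compared with SCS-only areas and with areas that have neither, so SCS-only comparators are foreseen.
- Coroner and paramedic services (Aim 3): the data agreements cover event data "including toxicology, temporal information, and geographic locations".

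**The concern.** Opening SCS first separates the two start dates. It does not separate the second year of SCS from the first year of DCS, because at every DCS site these are the same period. With a one-year lead and annual incidence, each DCS site supplies about one SCS-without-DCS observation, three in all. A present/absent term then assumes that SCS had its full effect from the day it opened.

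A new service may build up its clientele. The article itself speaks of SCS scale-up (Conceptual framework) and expects co-located DCS to raise uptake of other harm reduction services (Results). If the SCS effect strengthens after year one, the model has only the DCS term in which to put the difference at those sites.

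Among the analyses of recorded overdoses, this is the one stated to adjust for underlying trends, and it bears directly on the study's overall goal. A maturing SCS could therefore be reported as an independent benefit of DCS.

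**Working it through.** **The plan's own figures.** The article gives no effect size, power or error rate for this analysis, so there is nothing to reproduce. Its event counts agree with one another: 1002 calls near the DCS sites at 31% of the city total gives 1002/0.31 = 3232 a year, and the six-month counts give 2 × (1542 + 111) = 3306. Per DCS site, 1002/3 = 334 events a year.

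**Model.** For area i in year t: log E(Y) = area effect + year effect + β·SCS + δ·DCS, both services coded 0/1. This gives the same slope estimates as the conditional fixed effects Poisson model. The model is fitted to expected counts with a true DCS rate ratio (RR) of 1, so exp(δ) is the value the planned estimate converges to.

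**Assumptions not in the documents.** SCS RR of 0.95 in the first year and 0.85 afterwards; 0, 3 or 6 SCS-only areas opening at the same time as SCS at the DCS sites; a set of areas with neither service; SCS from 2018 and DCS from 2019; a common trend.

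**No SCS-only areas.** β is fixed by the single SCS-only year at the DCS sites, so β = ln 0.95. Later years there require β + δ = ln 0.85. Hence exp(δ) = 0.85/0.95 = 0.895, and all of the growth goes to DCS.

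**With SCS-only areas.** A single β must now fit 0.95 in the first year and 0.85 in later years of the SCS-only areas, so it settles in between and δ takes up the remainder.

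| SCS-only areas | Fitted DCS RR (true value 1) | Share of log growth credited to DCS |
|---|---|---|
| 0 | 0.89-0.90 | 100% |
| 3 | 0.93-0.95 | 46-65% |
| 6 | 0.95-0.96 | 37-46% |
| any, SCS effect constant | 1.00 | no growth |

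The share is ln(fitted RR)/ln(0.895). For example, ln 0.93/ln 0.895 = 0.0726/0.1112 = 65%, and ln 0.96/ln 0.895 = 0.0408/0.1112 = 37%. The ranges reflect different area sizes and study years; other layouts move the values by 0.01 to 0.02.

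**Other growth patterns.** For SCS RR 0.95 then 0.90, the fitted DCS RR is 0.947, 0.965-0.974 and 0.973-0.982 with 0, 3 and 6 SCS-only areas. For 0.95 then 0.80 it is 0.842, 0.890-0.919 and 0.913-0.942.

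**Time since opening.** If SCS is entered by year since opening and SCS-only areas are present, the fitted DCS RR is 1.000. With no SCS-only areas and a common one-year lag, the DCS column equals the sum of the columns for SCS year two onwards, so the two effects cannot be told apart.

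**Three treated areas.** In 1000 simulations per setting (true DCS RR 1, constant SCS RR 0.90, three SCS-only areas, assumed area-year variation beyond Poisson), the nominal 5% test rejected as follows:
- Poisson model-based errors: 4.8% with no extra variation, 11-13% at a coefficient of variation (CV) of 5%, 28-30% at 10% and 45-46% at 15%.
- Area-clustered errors: 12-17%.
- Quasi-Poisson scaling: 5-23%.

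Clustering alone therefore does not restore 5% with three treated areas.

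**The case against.** The bias is neither certain nor total. If SCS acts at full strength from opening, it is zero. The article plans SCS-only comparators in its spatial analysis, and the Poisson section compares the change with that in other areas; such comparators absorb part of the growth. A reader might infer that every bit of SCS growth is credited to DCS. That is true only if no SCS-only areas enter the model, and the documents do not support it as a general statement.

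A reader might also infer that the analysis will use Poisson model-based errors and so reject far too often. The article names the model but no variance estimator, and robust errors are compatible with its wording. That detail may sit in a fuller document, so no fault is alleged there. What stands is that three treated areas make inference fragile under the usual choices.

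The annual time unit is partly inferred: "the influence of DCS on the annual incidence of fatal and non-fatal overdose events will be characterized" does not fix the rows of the model or the coding of the launch year. Also, the stated primary outcome is self-reported overdose under Aim 1, and an individual-level substudy compares SCS clients with and without DCS.

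Finally, the difficulty is disclosed. But both sections go on to treat the one-year stagger as its solution, and that step is what fails.

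**Conclusion.** The concern holds in this form: a one-year SCS lead with adjustment only for SCS presence does not identify an independent DCS effect unless the SCS effect is constant from opening, and the article does not state that assumption. Under the assumed growth from 0.95 to 0.85, a DCS with no effect would show a rate ratio of about 0.89-0.90 with no SCS-only areas, 0.93-0.95 with three and 0.95-0.96 with six. The direction follows from the design; the size rests on the assumed growth and on the number of SCS-only areas, which the article does not give. Describing the experiment as ideal and the effect as independent claims more than the analysis can deliver. The point should be corrected before the analysis is run. It does not touch the Aim 1 primary analysis.

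**What to change.** In the longitudinal section of Aim 3:
- Make SCS-only areas the main comparator and state how many there are.
- Enter SCS by time since opening instead of present/absent.
- Use monthly or quarterly counts with the actual SCS and DCS opening dates.
- Use small-number inference that allows for extra-Poisson variation, for example permutation of DCS status across SCS areas where their number permits, and report its resolution. With three DCS and three SCS-only areas there are 20 assignments, so the smallest p-value is 1/20 = 0.05 one-sided and 0.10 for a symmetric two-sided test.

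There and in Limitations, replace the claims of an ideal natural experiment and an independent effect with: *the effect of adding DCS to SCS, assuming SCS matures in parallel in DCS and SCS-only areas*. Add that without SCS-only areas the two effects cannot be separated.

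The cost is rewording, modest programming and wider intervals. The data agreements already cover event times and locations.

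If SCS-only areas turn out to be few or absent, the remedy is correspondingly weak, and the article should say so.

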#### Spatial patterns of fatal and non-fatal overdose in Toronto (Aim 3)

Employing approaches previously used to assess the association between risky drug-related behaviors and frontline services [55], data from the OCC and TPaS will be used to assess the spatial association between frontline harm reduction agencies with DCS and overdose events. This will be done by comparing geographic units that have DCS and SCS co-located with sites that only have SCS located, compared with sites that have neither. Changes over time in the incidence of overdose in these units will be determined by employing geographic information systems approaches. First, spatial buffers around each DCS site will be generated, and TPaS and OCC data will be used to capture the spatial location of non-fatal and fatal overdoses in surrounding areas. Significance testing will then be done by analyzing dissemination blocks (the smallest geographic unit defined by Statistics Canada with a population of 400–700 people). Toronto experienced 1542 non-fatal and 111 fatal overdoses over a recent 6-month period (August 2017–February 2018), and based on existing spatial data, it is estimated that the range of annual overdose events per dissemination block will range from 0 to > 100. This exploratory approach represents a simple descriptive test to determine the spatial correlation of overdoses and DCS. Second, to further account for potential confounding of the association between DCS and spatial patterns of overdose as a result of co-location of SCS and DCS [56], the mean distances between fatal overdoses (OCC data) in neighborhoods in which SCS are implemented but have not yet implemented DCS will be compared. Third, geographically weighted regression (GWR) will be employed to determine the spatial heterogeneity between the location of overdoses (dependent variable) and location of DCS (independent variable), while accounting for the presence of SCS as above. GWR calculates local spatial statistics by fitting a weighted regression equation for each dissemination block in the study area to assess local variation [57]. Local statistics will then be compared with the global statistic for the entire geographic area (i.e., the Province of Ontario), and blocks exhibiting local variation differing from the global statistic will be identified (including by undertaking a sub-analysis restricted to blocks within the City of Toronto). Using GWR, it will be determined whether those blocks exhibiting local variation in overdose incidence are more or less likely to also contain DCS. Fourth, the local annual incidence rate of overdose for each block will be determined. The Wilcoxon signed rank-test has previously been shown to be effective at assessing fluctuations in the annual rate of fatal and non-fatal overdose [56], and will allow a determination of slope differences in the overdose rate in blocks that do and do not have DCS.

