
### Approach

By employing complementary data sources—including data from analysis of drug samples, quantitative intake and post-test surveys, SCS, coroners, paramedic services, and qualitative interviews—this study will comprehensively evaluate the impact of DCS on a range of policy-relevant drug-related outcomes, while considering the impacts of co-located SCS (refer to Table 1: Measures, Outcomes, and Data Sources). A mixed-methods approach followed by a meta-inference process will be used to maximize multiple data sources and synthesize results of quantitative and qualitative analyses.

**Table 1 Tab1:** Measures, outcomes, and data sources

Measures and outcomes	Data sources
Aim 1: Evaluate the impact of DCS access on changes in and factors influencing overdose and related risk behaviors	
Self-reported overdose among those that access DCS and those that do not	– Quantitative survey data (intake) – SCS client data
Proportion of participants reporting increase in protective behaviors (not using alone, carrying naloxone, use of SCS, consultation with staff, smaller/) “tester” dosage, discarding toxic substances)	– Quantitative survey data (intake/post-test) – SCS client data
Proportion of participants reporting they gained, intend to use, and/or used knowledge and skills	– Quantitative survey data (post-test) – Qualitative interviews
Aim 2: Investigate the perceived capacity of DCS to prevent overdose	
Characterize participant perceptions on the capacity of DCS to alter the risk of overdose	– Qualitative interviews
Identify participant perceptions of contexts, facilitators, and barriers to the use of DCS	– Qualitative interviews
Aim 3: Identify trends in the composition (qualitative and quantitative) of the unregulated drug supply in Toronto	
Number of analysis results detecting composition different from participant expectations	– Quantitative survey data (intake) – Drug sample analysis data
Increase in accuracy and timeliness of alerts in response to dangerous drug trends	– Drug sample analysis data – Qualitative interviews
Spatial association between frontline harm reduction agencies with DCS and fatal overdose, and changes over time	– First responder and coroner data (from OCC and TPaS)

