#### Estimated overdose incidence (Aim 3)

While no formal estimates of the overdose rate among people who use drugs in Toronto have been derived, 1002 overdose calls (fatal and non-fatal combined) were made to Toronto Paramedic Services between January 2018 and December 2018 in neighborhoods adjacent to the three frontline DCS sites, representing 31% of all calls across Toronto [49]; these neighborhoods are also those with the greatest density of people who use drugs [35]. We also note that the incidence of > 1000 overdose events recorded near DCS sites implies a relatively high event rate among potential DCS clients.

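### The GWR step takes Ontario as its reference although the only named non-fatal source is Toronto's, and it relates overdose level, not change, to DCS location

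*Protocol article*

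**What the plan says.** The section on spatial patterns (Aim 3) has four steps. The third fits a GWR with overdose location as the dependent variable and DCS location as the independent variable, accounting for SCS presence. The reference is provincial: "Local statistics will then be compared with the global statistic for the entire geographic area (i.e., the Province of Ontario"). The same sentence adds a city-level run, "including by undertaking a sub-analysis restricted to blocks within the City of Toronto". The step then asks "whether those blocks exhibiting local variation in overdose incidence are more or less likely to also contain DCS".

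On sources, the section on coroner and paramedic services says: "Data-sharing agreements with the Office of the Chief Coroner for Ontario (OCC) and Toronto Paramedic Services (TPaS) will cover both de-identified individual- and aggregated-population level" records. No paramedic service outside Toronto is named. The spatial section uses both sources: "TPaS and OCC data will be used to capture the spatial location of non-fatal and fatal overdoses in surrounding areas". Table 1 words the spatial outcome more narrowly, as "Spatial association between frontline harm reduction agencies with DCS and fatal overdose, and changes over time", yet lists both the coroner and the paramedic service as its data sources.

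On site placement, the section on estimated overdose incidence reports 1002 overdose calls in 2018 in the neighborhoods next to the three sites, 31% of Toronto's calls, and adds that "these neighborhoods are also those with the greatest density of people who use drugs". The abstract dates the DCS launch to 2019.

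**The concern.** There are two separate problems.

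**Coverage.** Coroner data reach the whole province, but the named paramedic data come from one city. A provincial statistic for an outcome that includes paramedic-attended events then compares an area where those events are recorded with an area where they are not. Toronto blocks would differ from the global value because of the source, not because of overdose risk.

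**Level rather than change.** The sites stand where overdose was already concentrated. A regression of overdose location on DCS location, with no stated time term, picks up that earlier concentration together with any effect of DCS. A positive association could be read as DCS failing, or doing harm, when it reflects where the agencies are.

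At stake is the reading of one spatial analysis that draws its own inference about DCS.

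**Working it through.** **Consistency of the plan's own figures.** No sample size or power is stated for the GWR, so there is none to reproduce. The two event totals can be compared. From the 2018 calls, 1002 / 0.31 = 3232 Toronto calls per year. From the spatial section, "Toronto experienced 1542 non-fatal and 111 fatal overdoses over a recent 6-month period", so (1542 + 111) × 2 = 3306 per year. These differ by 2.3%, so the inputs are coherent.

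**1. Coverage**

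Inputs: 1542 non-fatal and 111 fatal Toronto overdoses in six months (spatial section); 308 opioid-related deaths in Toronto and 1265 in Ontario in 2017 (Background).

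Assumptions: both event types are pooled, non-fatal events outside Toronto are absent from the count, and the true non-fatal-to-fatal ratio is the same elsewhere in Ontario.

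- Non-fatal share of Toronto's recorded events: 1542 / (1542 + 111) = 1542 / 1653 = 93%.
- Inflation of Toronto's rate relative to the rest of Ontario = Toronto's fatal plus non-fatal events / Toronto's fatal events. The population shares and the rest-of-Ontario deaths (1265 − 308 = 957) cancel.
- Six-month counts: 1653 / 111 = 14.9.
- 2017 deaths with annualised non-fatal events: 1542 × 2 = 3084; (3084 + 308) / 308 = 3392 / 308 = 11.0.
- Toronto's share of Ontario events: 308 / 1265 = 24.3% on deaths alone; 3392 / (3084 + 1265) = 3392 / 4349 = 78.0% on the pooled count.

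For coroner deaths alone, and for the run restricted to Toronto, this artefact is nil.

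**2. Level**

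Input: 31% of Toronto calls near the sites in 2018. The share *f* of Toronto's population living there is not in the document, so it is assumed and varied.

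Pre-DCS rate ratio against the rest of the city: RR = (0.31 / f) / (0.69 / (1 − f)). After a true reduction e near DCS sites it becomes RR × (1 − e). The reduction that brings it to 1 is 1 − 1/RR.

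| f (assumed) | Pre-DCS RR | RR after a 30% reduction | RR after a 50% reduction | Reduction needed to reach 1 |
|---|---|---|---|---|
| 5% | 8.54 | 5.98 | 4.27 | 88% |
| 10% | 4.04 | 2.83 | 2.02 | 75% |
| 15% | 2.55 | 1.78 | 1.27 | 61% |
| 20% | 1.80 | 1.26 | 0.90 | 44% |
| 25% | 1.35 | 0.94 | 0.67 | 26% |

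A Poisson simulation with a true 30% reduction agrees. The level contrast gave 5.96, 2.82 and 1.26 at f = 5%, 10% and 20%, while the before/after contrast gave 0.69 to 0.70. The simulation is not a fitted GWR and has no SCS term. It shows the direction of the problem, not the bias in the planned coefficient.

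**The case against.** The strongest defence is that the text permits a sound reading: an Ontario-wide GWR on coroner deaths, with the Toronto run for the outcomes that need paramedic data. Table 1 names fatal overdose, and the second spatial step uses coroner deaths. Under that reading there is no coverage artefact. This stands as a possibility, but the document does not settle it. Table 1 lists the paramedic service as a source, the section covers both event types, and the dependent variable is simply the location of overdoses. A reader might infer that non-Toronto blocks enter with zero non-fatal events; the text does not say how they are coded. If they are instead missing, no provincial benchmark for non-fatal events exists at all.

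Second, the 11- and 15-fold figures are crude Toronto-versus-rest gaps, not the bias in a local GWR coefficient. That is correct.

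Third, the model accounts for SCS presence, and all three DCS sites are co-located with SCS. A contrast with SCS-only blocks could be smaller than the table suggests, by an amount the document does not let one compute. The SCS term still supplies no pre-DCS baseline.

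Fourth, change is analysed elsewhere: the conditional fixed effects Poisson model in the longitudinal analysis compares before with after, and the fourth spatial step looks at slope differences. This limits the reach of the point but does not repair the GWR step. Nor does the exploratory label, which is attached to the first step, whereas the GWR is given its own question about DCS.

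**Conclusion.** The concern holds for the GWR step. On coverage, the provincial reference fits coroner deaths only. The 11- to 15-fold inflation is conditional on pooling and on the other assumptions stated with the calculation. On level, the step as written cannot separate a DCS effect from the concentration of overdose that preceded the launch. With 5% to 20% of Toronto's population assumed to live near the sites, a crude positive association survives a true 30% reduction; at 25% it does not.

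A reader might go further and infer that DCS blocks will appear as hot spots whatever DCS achieve. The figures do not support that: a large enough reduction removes the excess, and the SCS term may absorb part of it. Nor does Aim 3 lack an analysis of change. The primary outcome, self-reported overdose under Aim 1, is untouched.

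**What to change.** 1. Make the City of Toronto the main study area and the global reference for any outcome that uses paramedic data. This promotes the run already planned as a sub-analysis. Keep Ontario as the reference for coroner-recorded deaths only.
2. Reconcile Table 1 with the spatial section: state whether the spatial outcome is fatal overdose or both event types, and which source serves each.
3. Then choose one of two courses for the GWR:
   - Fit it to pre-to-post change in a form that tolerates zero counts, for example a Poisson GWR of post-DCS counts adjusted for pre-DCS counts, or a rate difference. Run the same model on pre-DCS years as a check. A block-level log rate ratio is unsuitable, because blocks hold 400–700 people and the plan expects annual counts that start at 0.
   - Or label the step descriptive and draw no conclusion from it about the effect of DCS.

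The cost is revised wording and slightly more analysis work. There would be no provincial benchmark for non-fatal events, but the named sources cannot supply a valid one in any case.

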To date, evaluations of DCS have been limited to “recreational drug users” in nightlife settings in Europe [19, 31, 32], and no DCS employing LC- or GC-MS analysis for point of care services and operating within SCS have been scientifically evaluated. Herein, we describe the methodology for a study assessing the impact of a multi-site DCS network in Toronto. The overall goal of the this study is to determine whether access to DCS, to be co-located with SCS at three frontline harm reduction agencies in Toronto, is associated with a reduction in the incidence of overdose and related risk behaviors resulting from the consumption of unknown or toxic unregulated drugs by people who use drugs accessing frontline services, including young people who use drugs. The study has three specific aims: (1) evaluate the impact of DCS access on changes in and factors influencing overdose and related risk behaviors, (2) investigate the perceived capacity of DCS to prevent overdose, and (3) identify composition (qualitative and quantitative) trends in Toronto’s unregulated drug supply. Given the limited evidence on the influence and impact of DCS for subpopulations of people who use drugs regularly or by injection, this research study will represent a novel contribution to the scientific literature and provide important insights on DCS as an overdose prevention intervention. The protocol and rationale for this study is itself an important contribution to the literature, as it provides full study transparency and will be useful to researchers planning to evaluate DCS in other jurisdictions.

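### The fourth spatial step merges the section's three groups into blocks with and without DCS and does not account for SCS, so its slope difference can mix the SCS effect with the DCS effect

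*Protocol article*

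**What the plan says.** All quotes are from the Protocol article.

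- **Opening of the spatial section (Aim 3).** The association between DCS sites and overdose will be assessed by "comparing geographic units that have DCS and SCS co-located with sites that only have SCS located, compared with sites that have neither".
- **Second step.** It is added "to further account for potential confounding of the association between DCS and spatial patterns of overdose as a result of co-location of SCS and DCS".
- **Third step (geographically weighted regression).** It relates overdose location to DCS location "while accounting for the presence of SCS as above".
- **Fourth step.** An annual overdose rate is computed for each dissemination block. The plan then says "The Wilcoxon signed rank-test has previously been shown to be effective at assessing fluctuations in the annual rate of fatal and non-fatal overdose", and that the test "will allow a determination of slope differences in the overdose rate in blocks that do and do not have DCS". SCS does not appear.
- **Longitudinal analysis (Aim 3).** The conditional fixed-effects Poisson model compares areas with and without DCS "while adjusting for the presence of SCS".
- **Background.** The study concerns "access to DCS, to be co-located with SCS at three frontline harm reduction agencies in Toronto", so every DCS site is also an SCS site.
- **Limitations.** The authors write that "we note challenges in disentangling the impact of SCS and DCS on overdose incidence and related behaviors given that these two interventions will be co-located". They rely on SCS having started one year before DCS to separate the two services.

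**The concern.** The plan treats separating DCS from SCS as a central difficulty, and each of the other analyses named above makes some provision for it. The fourth step makes none. On its wording, one side of the comparison holds only blocks with both services. The other side pools SCS-only blocks with all blocks that have neither. A signed-rank test takes no covariate, so SCS cannot be adjusted for inside it.

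The study's overall goal is to learn whether access to DCS is associated with fewer overdoses. A slope difference between blocks with and without DCS would naturally be read as evidence on that question. If SCS bent the overdose trend around its sites, or changed where events are recorded, part of that would show up in this comparison.

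**Working it through.** The plan gives no effect size, power, number of blocks, number of SCS-only sites or calendar window for this step, so there is no stated figure to reproduce. The check is algebraic, followed by a small illustration with assumed inputs.

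**1. What the two-group contrast estimates.** Let D be the effect of DCS on the log-rate slope, S the effect of SCS on that slope (assumed equal wherever SCS operates), and q the share of non-DCS blocks that have SCS only. Apart from a common trend:

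- DCS blocks (all with SCS): D + S
- non-DCS blocks: qS
- expected difference: D + S(1 − q)

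If the comparator is SCS-only units, q = 1 and the contrast reduces to D. If nearly all comparator blocks have neither service, q is near 0 and the contrast is near D + S.

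**2. How large q might be.** The plan describes dissemination blocks as units of 400 to 700 people, so there are many of them. Assume 0 to 10 SCS-only blocks among 100 to 3,000 non-DCS blocks:

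- 10 of 100: 1 − q = 0.90
- 10 of 3,000: 1 − q = 0.997
- 0 of any number: 1 − q = 1.00

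Under these assumptions, 90% to 100% of any SCS effect on the slope stays in the contrast.

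**3. What that does to the slope when D = 0.** Put the SCS start at year 0 and the DCS start at year 1 (the plan's one-year lag), and end the window at year 4. Fit a least-squares line to the annual log rate, with q ≈ 0. Two assumed shapes for the SCS effect:

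- one-time 20% drop: log 0.8 = −0.2231 in every year from year 0
- 10% drop growing each year: (t + 1) × log 0.9 from year 0, with log 0.9 = −0.1054

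The slope is Σ(t − t̄)s(t) / Σ(t − t̄)².

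| Window (years) | One-time 20% drop: slope | Annual rate ratio | Growing 10% a year: slope | Annual rate ratio |
|---|---|---|---|---|
| −3 to 4 | −0.2231 × 7.5/42 = −0.0398 | 0.961 | −0.1054 × 32.5/42 = −0.0815 | 0.922 |
| −2 to 4 | −0.2231 × 5/28 = −0.0398 | 0.961 | −0.1054 × 25/28 = −0.0941 | 0.910 |
| −1 to 4 | −0.2231 × 2.5/17.5 = −0.0319 | 0.969 | −0.1054 | 0.900 |
| 0 to 4 | 0 | 1.000 | −0.1054 | 0.900 |

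Every ratio below 1 here is spurious, because DCS was given no effect. A q of 0.10 would change little: 0.961 raised to the power 0.9 is 0.965.

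**4. What decides the size.** A one-time SCS change that is complete before the window opens drops out of a slope. A change inside the window, or one still growing, does not. The step fixes neither the window nor a restriction that would secure the harmless case.

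**The case against.** The strongest reply is that the three-group sentence opens the section and can govern all four steps. The sentence after it refers changes over time back to those same units, and the fourth step is a change-over-time step. In a condensed article, not repeating the grouping in a closing sentence is weak evidence that it was dropped. That reading is possible. Against it, the third step takes care to restate how it handles SCS, while the fourth names a different, two-way split. This is a stated contrast that does not match the section's own design, rather than a detail left out, and it needs to be reconciled.

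Four stronger readings are tempting, and the document does not support them:

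- **That the control was SCS-only units and has been widened.** Units with neither service are in the design from the opening sentence. The fourth step merges two comparison groups that were already there.
- **That the step's result is simply the combined effect of both services.** SCS came first, and the comparator may contain some SCS-only blocks. As the table shows, the SCS share can be zero.
- **That the step credits the difference to DCS.** It promises only to determine slope differences, in a section framed as spatial association. The claim to an independent DCS effect belongs to the Poisson analysis, which adjusts for SCS.
- **That an SCS change of 10% to 30% would appear here as a ratio of 0.70 to 0.90.** Those are ratios of levels. The step compares slopes, and a one-time 20% drop moves the annual ratio only to about 0.96 to 0.97.

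It is also fair to say that a contrast limited to SCS-only comparators would rest on very few units. If each of the three DCS sites lies in one block, a signed-rank test on three blocks cannot give a two-sided p below 2/2³ = 0.25.

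**Conclusion.** The point holds in a limited form. As worded, the fourth step contrasts blocks with and without DCS and makes no provision for SCS, so its slope difference can mix the two effects and cannot by itself be read as the effect of DCS. With no DCS effect, the spurious annual rate ratio is about 0.96 to 0.97 for a one-time 20% SCS drop when the window includes pre-SCS years, 1.00 when it starts in the first SCS year, and about 0.90 to 0.92 if the SCS effect grows by 10% a year.

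The SCS effect sizes, windows and block counts are assumptions. That most non-DCS blocks have neither service is a presumption from the small size of the blocks. The co-location and the one-year lag are the plan's own. The defect is confined to one of four spatial steps and does not touch the SCS-adjusted Poisson analysis. It should be corrected, but it does not undermine the study.

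**What to change.** In the fourth step:

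1. Keep the three groups with which the section opens.
2. Base any statement about DCS on DCS+SCS versus SCS-only units, comparing the change from the SCS-only period to the DCS period, and state that window.
3. Report DCS+SCS versus neither separately, labelled as the combined effect of both services.
4. Present the step as descriptive, and say that the SCS-adjusted Poisson model carries the inference on the independent effect of DCS.

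The coroner and paramedic data already planned are sufficient, so the change is to the analysis wording. The price is precision: with three DCS sites and few SCS-only units, the DCS contrast will be imprecise and a rank test on it may have almost no power. It also assumes that SCS acts alike in the two groups being compared, which should be said when the result is reported.
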